### Adverse events

3.2

We shall document any adverse events that happen throughout the trial ensuring that patients receive prompt medical attention at our facilities or at local hospitals. Interim analyses are conducted to facilitate decisions on either halting or proceeding with the trial based on the data that has been accumulated.

### Statistical analysis

3.3

Appropriate statistical methods, such as Fisher’s exact test or Pearson’s chi-squared test, will be employed for the analysis of categorical data. Continuous variables will be compared by an independent samples Student’s *t*-test or Mann–Whitney *U*-test, as appropriate. We will present the cumulative incidence of stroke or mortality over a 12-month maximum follow-up period using Kaplan–Meier analysis, and we will determine the hazard ratios along with their 95% confidence intervals through the application of Cox proportional hazards modeling and the log-rank test to assess the efficacy of the treatment. Statistical significance is defined as a *p* value of < 0.05.

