**Methods and analysis:**

This is a prospective, randomized, open-label, blinded end-point study, which will assess the efficacy and safety of evolocumab in patients with symptomatic ICAS. Eighty patients who suffer a stroke/transient ischemic attack (TIA) caused by ICAS recently will be randomly allocated in a 1:1 ratio to the evolocumab plus statin treatment group or the statin treatment group. High resolution vessel wall magnetic resonance imaging (HR-vwMRI) will be performed at recruitment and after 6 months and 12 months. The primary outcome is changes in plaque characteristics assessed by HR-vwMRI at 6th month and 12th month after treatment. Cognitive and neurological function will also be evaluated at recruitment and follow-up. This trial is being conducted at the first affiliated hospital of Nanjing medical university, China.

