### Study design

2.1

This is a prospective, randomized, open-label, and blinded endpoint assessment study. We will recruit 80 patients who have recently suffered a stroke/transient ischemic attack (TIA) due to ICAS. The inclusion and exclusion criteria are shown in Tables 1, 2, respectively. Patients will be allocated in a 1:1 ratio to the evolocumab plus statin treatment arm or the statin alone treatment arm. Evolocumab (150 mg) will be injected subcutaneously every 2 weeks for 12 months. Both arms will receive statins for 12 months, including atorvastatin 20–80 mg or rosuvastatin 10–20 mg. According to current guideline and the standards in SAMMPRIS study, optimal medical management with aggressive control of the risk factors will be provided to all patients, such as proper application of antiplatelet, antihypertensive, and antidiabetic drugs. HR-vwMRI will be performed at baseline and at 6th and 12th month after recruitment. Blood test will be conducted at baseline and at 1st, 3rd, 6th, and 12th month after recruitment. National Institute of Health Stroke Scale (NIHSS), modified Rankin Scale (mRS), Barthel index, Mini-Mental State Examination (MMSE), and Montreal Cognitive Assessment (MoCA) will be evaluated at baseline and at 3rd, 6th, and 12th month post-recruitment. This study was approved by the ethics board of the first affiliated hospital of Nanjing Medical University. Written informed consents will be obtained. The flow chart of this study is shown in Figure 1.

**Table 1 tab1:** Inclusion criteria.

1. Age ≥30 years and ≤75 years
2. TIA or acute ischemic stroke that occurred within 6 weeks prior to randomization
3. Modified Rankin score of ≤4
4. TIA or acute ischemic stroke attributed to a 50 to 99% stenosis of a major intracranial artery [internal carotid artery (ICA), vertebral artery (VA), basilar artery (BA) and the M1 segment of middle cerebral artery (MCA)]. The diagnostic evaluation for ICAS at each site is confirmed by the local investigator, using high resolution MR
5. To increase the likelihood that the symptomatic intracranial stenosis is atherosclerotic, patients aged 30–49 years are required to meet at least one additional criteria (i–vi) below:
o Insulin dependent diabetes for at least 15 years

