### Study outcomes

3.1

Primary endpoints:

1) Changes in plaque enhancement.

A reduction of ≥ 1 grading in plaque enhancement after 12 months’ treatment was regarded as relief of plaque enhancement. For example, a patient’s plaque enhancement reduces to grade 1 or even 0 after 12 months’ treatment, compared to grade 2 at the time of enrollment.

2) Changes in degree of stenosis.3) Changes in plaque enhancement ratio.4) Changes in plaque burden.5) Changes in hypoperfusion volume.6) T1 hyperintensity.

We define three types of T1 hyperintensity changes at 12 month after recruitment: type A, no changes before and after treatment; type B, disappearance of T1 heperintensity; type C, new T1 hyperintensity.

7) Changes in remodeling index (RI) of the plaque.

Secondary endpoints:

1) Recurrent stroke (ischemic or hemorrhagic) or death during follow-up.2) Changes in LDL-cholesterol levels.3) Changes in NIHSS/Barthel index/mRS score.4) Changes in MoCA/MMSE score.

All changes above before and after treatment in each arm will be calculated and compared between arms.

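### The two-sample tests named for the continuous plaque changes leave the month-6 scan and the baseline value out of the month-12 comparison; a baseline-adjusted repeated-measures model would use both

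*Protocol article*

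**What the plan says.** On imaging, the Study design section of the protocol article states: "HR-vwMRI will be performed at baseline and at 6th and 12th month after recruitment". The abstract places the primary outcome at both follow-up visits: "The primary outcome is changes in plaque characteristics assessed by HR-vwMRI at 6th month and 12th month after treatment".

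Under Study outcomes, two of the seven primary endpoints are tied to month 12. For enhancement grade: "A reduction of ≥ 1 grading in plaque enhancement after 12 months’ treatment was regarded as relief of plaque enhancement". For T1 hyperintensity: "We define three types of T1 hyperintensity changes at 12 month after recruitment". The continuous features (degree of stenosis, enhancement ratio, plaque burden, hypoperfusion volume, remodeling index) are listed as changes without a visit. The list closes with "All changes above before and after treatment in each arm will be calculated and compared between arms".

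Under Statistical analysis, the method for these changes is "Continuous variables will be compared by an independent samples Student’s" t-test or the Mann–Whitney U-test, whichever is appropriate. Categorical data get methods such as Fisher's exact or Pearson's chi-squared test. The only named methods that keep partial follow-up are Kaplan–Meier, Cox and log-rank, and those are for stroke or death.

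**The concern.** A t-test or Mann–Whitney test takes one value per patient. For the month-12 comparison that value is the change from baseline to month 12. A patient scanned at month 6 but not at month 12 has no such value, and the tests have no means of using the month-6 scan in its place. They also compare raw changes, without adjusting for where each plaque started.

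Two things are at stake. The first is precision, in a trial of only 40 patients per arm. The second is bias: if loss after month 6 differs between arms and is related to what the month-6 scan showed, the patients left at month 12 are no longer comparable between arms. The trial is open-label, so knowledge of the arm could affect who returns. The direction of such a bias cannot be read from the article.

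**Working it through.** **Inputs from the article.** Size: "We will recruit 80 patients who have recently suffered a stroke/transient ischemic attack (TIA) due to ICAS". Allocation: "Patients will be allocated in a 1:1 ratio to the evolocumab plus statin treatment arm or the statin alone treatment arm". Hence 80/2 = 40 per arm, with two follow-up scans per patient. The article gives no power calculation, effect size, SD, loss rate or correlation, so there is no stated figure to reproduce.

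**Assumptions.** A proportion d of each arm, 5% to 20%, has a month-6 scan but no month-12 scan. The correlation r between month-6 and month-12 change is 0.5 to 0.9. Tests are two-sided at 0.05 with SD 1. The only figure in the article near to a loss rate is in the Introduction: about one in five medically treated patients had recurrent stroke or death over 3 years. At a constant rate that is 1 − 0.8^(1/6) ≈ 3.7% per six months. It counts events, not missed scans, so it is a loose guide.

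**Precision.** The stated test uses n = 40(1 − d). A likelihood-based model with both scans has effective size n = 40 / [1 + (d/(1 − d))(1 − r²)].

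- d = 5%: stated test 38. Model: r = 0.5 gives 40/(1 + 0.0526 × 0.75) = 38.5; r = 0.9 gives 40/(1 + 0.0526 × 0.19) = 39.6.
- d = 10%: stated test 36. Model: 40/(1 + 0.1111 × 0.75) = 36.9; 40/(1 + 0.1111 × 0.19) = 39.2.
- d = 20%: stated test 32. Model: 40/(1 + 0.25 × 0.75) = 33.7; 40/(1 + 0.25 × 0.19) = 38.2.

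To express this as power, take the effect that 40 per arm detects with 80% power: (1.960 + 0.842) × √(2/40) = 0.626 SD.

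| Loss | Stated test | Model, r = 0.5 to 0.9 |
|---|---|---|
| 5% | 78.0% | 78.5–79.6% |
| 10% | 75.7% | 76.8–79.2% |
| 20% | 70.7% | 72.9–78.2% |

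These figures cover only the recovery of month-6 information. Any further gain from baseline adjustment depends on the correlation between baseline and follow-up values, which is not given, and is not sized here.

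**Bias: when it arises.** If leavers do worse than stayers by a deficit D, an arm's mean among those who stay differs from its full mean by d × D. The error in the difference between arms is therefore (d₁ − d₂) × D. With equal loss and the same deficit in both arms it is zero. With 15% against 5% and D = 1 SD (all assumed) it is 0.10 SD.

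**Bias: what the month-6 scan can repair.** Loss was simulated in one arm only, with the log-odds of loss rising by 1 per SD of month-6 change (400,000 simulated patients). Because the other arm loses nobody, this leans towards a worst case.

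| Loss in that arm | r = 0.5 | r = 0.7 | r = 0.9 |
|---|---|---|---|
| 10%, month-12 completers | 0.046 SD | 0.060 SD | 0.081 SD |
| 20%, month-12 completers | 0.086 SD | 0.123 SD | 0.155 SD |

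The model using month 6 was off by at most 0.004 SD in every cell. That result holds because loss was made to depend on the observed month-6 value. It says nothing about loss that follows worsening after that scan.

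**The case against.** The strongest objection is that this is only a missing-data rule that a journal article leaves to an analysis plan we do not have. A t-test can be run on imputed data, the article nowhere says that only completers will be analysed, and its test sentence is generic. This stands in part: the absence of an imputation rule is not raised here. What remains is the choice of test that the article does state. That test does not borrow from month 6 or adjust for baseline by itself.

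A reader might go further and infer that month-6 data are thrown away, or that the primary result will be a biased completers' analysis. The documents do not support that. The abstract puts the outcome at month 6 as well, so those scans would count in a month-6 comparison. Month 12 is fixed only for enhancement relief and T1 type, not for the continuous features. No loss rate is given, and nothing shows that loss will differ by arm. Retention also gets some attention: patients must agree to follow-up, those who have a procedure stay in follow-up for a year, and those unlikely to survive a year or unable to be followed reliably are excluded.

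It is also fair to object that a mixed model is no cure for every loss. Worsening between month 6 and a missed month-12 scan is not observed, and a plaque value after death is undefined rather than missing. A normal model may suit hypoperfusion volume poorly, since a volume above a threshold is plausibly skewed with many zeros. These objections stand, and they limit the fix below.

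**Conclusion.** The point holds as an improvement to a stated method. For the month-12 comparison of the continuous plaque changes, the named tests use neither the month-6 scan of a patient without a month-12 scan nor the baseline value as a covariate.

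The gain from using both scans is small if loss is low, about 0.5 to 1.6 patients' worth per arm at 5% loss, and moderate at 20% loss, about 1.7 to 6.2. Protection against bias matters only if loss differs by arm and tracks the month-6 result; in the one-arm simulation it was worth about 0.05 to 0.16 SD at 10–20% loss. Every loss rate, correlation and effect size behind these figures is assumed. The article does not show that the trial will be biased, or in which direction.

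**What to change.** In Statistical analysis:

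- **Degree of stenosis, enhancement ratio, plaque burden, remodeling index.** Replace the two-sample test by a repeated-measures mixed model of the month-6 and month-12 changes, with arm, visit, arm-by-visit, baseline and baseline-by-visit. Include every randomised patient with at least one follow-up scan, and report the month-12 contrast between arms.
- **Hypoperfusion volume.** Use a suitable transformation within that model, or a rank-based analogue.
- **Enhancement grade.** Bring in the month-6 grade through an ordinal or logistic repeated-measures model, or by multiple imputation. Count a missing month-12 grade as not relieved only as a sensitivity analysis. As the main rule it can create a difference: with true relief of 50% in both arms and loss of 15% and 5% unrelated to relief (assumed), the rates become 0.50 × 0.85 = 42.5% and 0.50 × 0.95 = 47.5%, a spurious 5 points.
- **Death.** State separately how patients who die before month 12 are handled, because the model would otherwise imply a plaque value for them.

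The cost is revised wording and a little more analysis, with no new scans or patients. The downside is that the model assumes loss depends only on observed values, and that assumption should be stated.

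### For the continuous endpoints the plan compares raw change scores with an unadjusted two-sample test; adjusting for the baseline value already collected would be more precise at no data cost

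*Protocol article*

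**What the plan says.** Two sentences of the protocol article together fix the analysis.

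- Study outcomes (3.1) sets the quantity: "All changes above before and after treatment in each arm will be calculated and compared between arms".
- Statistical analysis (3.3) sets the test: "Continuous variables will be compared by an independent samples" Student's t-test or by a Mann–Whitney U-test. Categorical data go to Fisher's exact or the chi-squared test. The only regression model named is Cox, for stroke or death.

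Baseline values will exist. Study design (2.1) states that "HR-vwMRI will be performed at baseline and at 6th and 12th month after recruitment", and that the neurological and cognitive scales "will be evaluated at baseline and at 3rd, 6th, and 12th month post-recruitment". The same section schedules blood tests at baseline and at months 1, 3, 6 and 12. No section names a model that includes a baseline value as covariate.

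**The concern.** Subtracting the baseline value adjusts for it with a slope fixed at 1. That is the best slope only if a patient one unit higher at baseline is expected to be one full unit higher at follow-up. Measurement error and regression to the mean usually make the slope smaller.

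The article gives reasons to doubt a slope of 1 for several endpoints:

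- The Introduction describes the drug's LDL effect as a proportion (around 60%), so absolute change should grow with baseline.
- Patients with TIA are eligible, and those at the floor of NIHSS or mRS cannot improve.
- Hypoperfusion volume cannot fall below zero.

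Two things are at stake in a trial of 80 patients, whose limited size the article itself acknowledges. The first is precision. The second is that a chance baseline difference between arms feeds into the estimated effect with a known sign.

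**Working it through.** **Inputs from the article.** Study design gives N = 80 ("We will recruit 80 patients who have recently suffered a stroke/transient ischemic attack (TIA) due to ICAS") and equal allocation ("Patients will be allocated in a 1:1 ratio to the evolocumab plus statin treatment arm or the statin alone treatment arm"), hence 40 per arm. The significance level is 0.05. Sidedness is not stated; two-sided is assumed, and this does not affect the variance ratio.

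**Inputs that are assumptions.** The article gives no baseline-to-follow-up correlation ρ, standard deviation, effect size or power. So ρ is shown from 0.3 to 0.9, and equal variance σ² at both visits is assumed. There is no figure in the plan to reproduce.

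**Step 1: variance.** Per patient:

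- change score: 2(1 − ρ)σ²
- ANCOVA (large sample): (1 − ρ²)σ²
- ratio, ANCOVA to change score: (1 − ρ²) / [2(1 − ρ)] = (1 + ρ)/2

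The fraction by which ANCOVA's variance is lower is (1 − ρ)/2.

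**Step 2: patients.** Extra patients a change-score analysis needs to match ANCOVA on 80: 80 × 2/(1 + ρ) − 80. For example, at ρ = 0.5 this is 160/1.5 − 80 = 26.7.

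**Step 3: power, for orientation.** Suppose the effect is such that the change-score test has 80% power. ANCOVA's power is then Φ(2.80 × √[2/(1 + ρ)] − 1.96).

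**Step 4: chance imbalance.** The SD of the baseline difference between arms is √(2/40) = 0.22 baseline SD. Given a baseline difference d, the change-score estimate shifts by −(1 − ρ)d. The last column gives the size of this shift for d of one such SD (0.224 before rounding).

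| Assumed ρ | Variance ratio | Lower by | Extra patients | ANCOVA power when change score has 80% | Shift (SD units) |
|---|---|---|---|---|---|
| 0.3 | 0.65 | 35% | 43 | 93.5% | 0.16 |
| 0.5 | 0.75 | 25% | 27 | 89.9% | 0.11 |
| 0.7 | 0.85 | 15% | 14 | 86.0% | 0.07 |
| 0.9 | 0.95 | 5% | 4 | 82.0% | 0.02 |

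**Step 5: finite-sample check.** In 20,000 simulated trials of 40 per arm, the variance ratio was 0.768, 0.866 and 0.966 at ρ = 0.5, 0.7 and 0.9. The small excess over theory is the cost of estimating the slope. On these ratios the extra patients are 80/0.768 − 80 = 24, 80/0.866 − 80 = 12 and 80/0.966 − 80 = 3. The change-score estimate moved by −0.49, −0.30 and −0.10 per unit of baseline difference. The ANCOVA estimate moved by 0.01 or less.

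**Step 6: stenosis.** In general, with X the baseline value and β its true slope, Var(change) = Var(ANCOVA) + (1 − β)²Var(X). Entry requires 50–99% stenosis, which restricts Var(X). The loss may therefore be smaller for stenosis than the table shows.

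**The case against.** The strongest objection is scope. This is a condensed article, its statistics paragraph is generic, and covariate adjustment is often left to an analysis plan that is not shown. That would settle the matter if the article were silent. It is not: it states both the quantity and the test, and the stated pair is the less precise choice.

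Several stronger readings are tempting, and the objection to each stands.

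- A reader might infer that every endpoint is affected. Recurrent stroke or death ("Recurrent stroke (ischemic or hemorrhagic) or death during follow-up") has no baseline value and is analysed as time to event. Primary endpoints 1 (relief of enhancement grade) and 6 (type of T1 hyperintensity change) are categorical.
- A reader might infer that baseline imbalance is left uncorrected, or that the result is biased. Subtraction does correct, but with the wrong slope. Over randomisation the comparison is unbiased; the bias is conditional on the imbalance that occurred. Regression to the mean and selection on stenosis act on both arms alike and do not bias the contrast.
- A reader might settle on one patient count, such as 14 to 27. That range needs ρ between 0.5 and 0.7, which nothing in the article supports.
- A reader might take ANCOVA to be always at least as precise. That holds in large samples; at 40 per arm there is a small cost.

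The figures are also normal-theory. They do not carry over directly to the Mann–Whitney test, to skewed hypoperfusion volume or to bounded scales.

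**Conclusion.** The point holds for the continuous change endpoints: stenosis, enhancement ratio, plaque burden, hypoperfusion volume, remodeling index, LDL cholesterol and the scale scores. The planned analysis is valid but inefficient, so this is a worthwhile improvement and not an error that invalidates the trial.

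The size of the gain depends on ρ, which has to be assumed. It is substantial if baseline and follow-up are weakly correlated and slight if they are strongly correlated. The direction does not depend on the exact value, except that near ρ = 1 the gain becomes negligible.

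**What to change.** For each continuous change endpoint, replace the two-sample test with a model of the follow-up value on arm plus the baseline value of that endpoint, and report the adjusted difference with its 95% CI. Modelling the change with baseline as covariate gives the same arm effect, so the endpoints can still be described as changes.

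- For hypoperfusion volume use a rank-based ANCOVA; a plain log is undefined where the volume is zero.
- For bounded scales such as mRS and NIHSS use an ordinal or rank-based model adjusted for baseline.
- Keep the t-test and Mann–Whitney comparisons as a sensitivity analysis.
- Do not add statin intensity as a covariate unless it was fixed before randomisation. In an open-label trial a dose chosen after allocation may depend on the arm.
- Leave the analyses of stroke or death and of primary endpoints 1 and 6 outside this change.

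The cost is analysis wording only, since the baseline measurements are already scheduled. The change should be made before outcome data are compared by arm.

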## Introduction

1

Intracranial atherosclerosis stenosis (ICAS) is one of the important causes of ischemic stroke occurrence and recurrence worldwide and is especially common in Asian (1, 2). It accounts for 30–50% of strokes in Asian, but only 5–10% in the West (3, 4). Aggressive medical management (e.g., high intensity statin therapy to reduce low-density lipoprotein (LDL) cholesterol <1.8 mmol/L) is superior to the percutaneous transluminal angioplasty and stenting for symptomatic ICAS in the SAMMPRIS study. However, around one in five patients still experienced stroke recurrence or death during 3-year follow-up in the aggressive medical treatment group (5).

As a fully human monoclonal antibody and a member of proprotein convertase subtilisin-kexin type 9 (PCSK9) inhibitors, evolocumab has the potential to decrease LDL cholesterol levels by around 60%. The FOURIER study showed that evolocumab decreased cardiovascular events (i.e., cardiovascular death, myocardial infarction, and stroke), in patients with atherosclerotic cardiovascular disease during 2.2 years follow-up (6). It’s still largely unknown whether evolocumab could affect the evolution of ICAS and reduce ischemic events in patients with stroke.

We thus designed this prospective, randomized, open-label, blinded end-point study to evaluate the effects of evolocumab added to statin therapy (EAST) in patients with stroke/transient ischemic attack (TIA) caused by ICAS. Eighty patients will be enrolled and assigned into two arms with or without evolocumab. Changes in plaque characteristics on high resolution vessel wall magnetic resonance imaging (HR-vwMRI), neurological function and cognitive function will be evaluated and analyzed between groups over a period of 1 year follow-up.

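### Stroke or death: with about three control-arm events expected, the planned Cox hazard ratio needs a sparse-event method and an exploratory label

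*Protocol article*

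**What the plan says.** Study outcomes (3.1) lists recurrent stroke or death first among the secondary endpoints; all primary endpoints are imaging measures. Statistical analysis (3.3) plans to show the "cumulative incidence of stroke or mortality over a 12-month maximum follow-up period using Kaplan–Meier analysis". It continues: "we will determine the hazard ratios along with their 95% confidence intervals through the application of Cox proportional hazards modeling and the log-rank test". The stated aim of this step is "to assess the efficacy of the treatment". A p value below 0.05 is the criterion for significance throughout.

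The size of the trial is in Study design (2.1): "We will recruit 80 patients", with 1:1 allocation. The only background event rate is in the Introduction, for the medical arm of an earlier stenting trial: "around one in five patients still experienced stroke recurrence or death during 3-year follow-up in the aggressive medical treatment group". The article gives no 12-month rate, no expected number of events, no target hazard ratio and no power for this endpoint.

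**The concern.** An ordinary Cox model estimates the hazard ratio by maximising the partial likelihood. If one arm has no events, that likelihood has no finite maximum: the estimate runs to zero or infinity, and the usual interval (estimate plus or minus a multiple of its standard error) does not exist. When both arms have events but only a few, the estimate is finite, but the normal approximation behind the interval is poor.

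With 40 patients per arm and 12 months, both situations are realistic. Two things are at stake. The first-listed secondary endpoint may end with no reportable hazard ratio, and this is more likely the better the drug works, because an empty evolocumab arm becomes more probable. Second, an analysis labelled as assessing efficacy and judged at p < 0.05 invites a non-significant result to be read as absence of effect.

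**Working it through.** The article states no event count or power for this endpoint, so there is no figure of its own to reproduce. The check derives the expected counts from its inputs.

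**Inputs.** 80 patients, 1:1, so 40 per arm (2.1). At most 12 months of follow-up (3.3). About 20% stroke or death over 3 years (Introduction). Assumptions: the 3-year rate carries over to this population, the hazard is constant, and nobody is lost before 12 months.

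**1. Expected events.** Hazard = −ln(0.8)/3 = 0.0744 per year. The 12-month risk is 1 − 0.8^(1/3) = 7.17%. Control arm: 40 × 0.0717 = 2.87 events. With no effect the total is 5.73. At a hazard ratio of 0.5 the evolocumab arm expects 40 × [1 − 0.9283^0.5] = 1.46.

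Patients enter within 6 weeks of a stroke or TIA, so risk may be front-loaded. An assumed 12-month risk of 12% gives 40 × 0.12 = 4.8 control events. If all 20% fell in year 1, there would be 40 × 0.20 = 8.

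**2. No finite hazard ratio.** With control risk p, P(no control events) = (1 − p)^40 and P(no evolocumab events) = (1 − p)^(40 × HR). At least one empty arm has probability a + b − ab, where a and b are these two.

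| 12-month control risk | True HR | a | b | At least one empty arm |
|---|---|---|---|---|
| 7.2% | 1 | 0.0510 | 0.0510 | 10.0% |
| 7.2% | 0.75 | 0.0510 | 0.1074 | 15.3% |
| 7.2% | 0.5 | 0.0510 | 0.2259 | 26.5% |
| 12% | 1 | 0.0060 | 0.0060 | 1.2% |
| 12% | 0.5 | 0.0060 | 0.0776 | 8.3% |
| 20% | 1 | 0.0001 | 0.0001 | 0.03% |
| 20% | 0.5 | 0.0001 | 0.0115 | 1.2% |

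Simulated trials at 7.2% agree: about 9% at a hazard ratio of 1 and 26% at 0.5.

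**3. The interval when the estimate is finite.** In the same simulations at 7.2%, standard 95% Wald intervals covered the true hazard ratio about 99.5% of the time. That figure is conditional on both arms having events. The intervals are therefore too wide for their nominal level.

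**4. The log-rank test.** In 10,000 simulated null trials per scenario, the two-sided 5% log-rank test rejected in 5.0% at a 7.17% risk, 5.2% at 10%, 5.0% at 12% and 4.9% at 15%. Its size is sound.

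**5. What remains computable.** With one empty arm, the Kaplan–Meier estimates and the log-rank test still exist. They give no comparison only if both arms are empty: 0.0510 × 0.0510 = 0.3% at a hazard ratio of 1, and 0.0510 × 0.2259 = 1.2% at 0.5. Firth-penalised Cox likewise needs only one event in total.

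**The case against.** The strongest reply is that Cox, log-rank and Kaplan–Meier are the standard tools for time to stroke or death, that a confidence interval shows imprecision openly, and that the choice of interval or of a sparse-event fallback belongs in an analysis plan that is not shown. Much of this stands. Section 3.3 does not say that the interval is a Wald interval; that is an assumption about what standard software prints. The article also limits its own reach: the endpoint is secondary, the hypothesis concerns plaque on imaging, the Discussion calls for larger multicentre studies, and the limitations section urges caution. But those cautions are general, while 3.3 itself names the estimator and attaches an efficacy purpose to it. That is stated, not omitted.

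Three stronger readings are tempting and should be resisted.

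- A reader might infer that the hazard ratio will often be inestimable. At the article's own rate it is finite in about 90% of trials under no effect and in roughly three quarters at a hazard ratio of 0.5; under higher first-year risk it is nearly always finite.
- A reader might infer that the log-rank test is invalid with so few events. Its size holds at 5%, so low counts give no reason to remove it. Whether to keep its p value is a matter of preference.
- A reader might treat the low power as a defect of the plan. Power at a hazard ratio of 0.5 is about 11% by the Schoenfeld approximation at 7.2%, and the interval around a hazard ratio of 1 is about 0.19 to 5.1. These figures describe the sample size, and the plan claims no power for clinical events. No change of estimator would make 80 patients informative about stroke or death.

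**Conclusion.** The point holds in a limited form. The estimator named for the first-listed secondary endpoint has a material chance of yielding no number at the only event rate the article offers, and its usual interval is miscalibrated at that rate. The purpose attached to it is also stronger than a handful of events can bear.

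The size depends on an assumption. The count of about three control events is not a figure in the article; it rests on carrying over a 3-year rate with constant hazard, and the plausible range is about 3 to 8. Toward the upper end the estimability problem all but disappears, and the case for the exploratory label carries most of the weight. The imaging endpoints are unaffected. Severity is low: a cheap improvement, not a threat to the trial's conclusions.

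**What to change.** In section 3.3, for stroke or death:

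- Report the number of events per arm, the Kaplan–Meier estimates, and the 12-month risk difference with a score-type or exact 95% interval.
- If a hazard ratio is given, estimate it by Firth-penalised Cox regression with a profile-likelihood interval. This stays finite when one arm is empty. State that no hazard ratio will be given if neither arm has an event.
- The log-rank test may stay.
- Replace the efficacy wording with a statement that this secondary endpoint is exploratory and that a non-significant p value will not be read as no effect.

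The cost is a few lines of text and standard software. The downsides are an estimator less familiar to readers and a softer label for a secondary endpoint. No extra patients, visits or data are needed.
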